## Abstract

**Background:**

Borderline Personality Disorder (BPD) is a complex and debilitating disorder, characterized by deficits in metacognition and emotion dysregulation. The “gold standard” treatment for this disorder is psychotherapy with pharmacotherapy as an adjunctive treatment to target state symptoms.

The present randomized clinical trial aims to assess the clinical and neurobiological changes following Metacognitive Interpersonal Therapy (MIT) compared with Structured Clinical Management (SCM) derived from specific recommendations in APA (American Psychiatric Association) guidelines for BPD.

**Methods:**

The study design is a randomized parallel controlled clinical trial and will include 80 BPD outpatients, aged 18–45 enrolled at 2 recruitment centers. Primary outcome will be the clinical change in emotion regulation capacities assessed with the Difficulties in Emotion Regulation Scale (DERS). We will also investigated the effect of psychotherapy on metacognitive abilities and several clinical features such as BPD symptomatology, general psychopathology, depression, personal functioning, and trait dimensions (anger, impulsivity, alexithymia). We will evaluate changes in brain connectivity patterns and during the view of emotional pictures. A multidimensional assessment will be performed at the baseline, at 6, 12, 18 months. We will obtain structural and functional Magnetic Resonance Images (MRIs) in MIT-Treated BPD (*N* = 30) and SCM-treated BPD (*N* = 30) at baseline and after treatment, as well as in a group of 30 healthy and unrelated volunteers that will be scanned once for comparison.

**Discussion:**

The present study could contribute to elucidate the neurobiological mechanisms underlying psychotherapy efficacy. The inclusion of a multidisciplinary study protocol will allow to study BPD considering different features that can affect the treatment response and their reciprocal relationships.

**Trial registration:**

NCT02370316. Registered 02/24/2015.

**Electronic supplementary material:**

The online version of this article (10.1186/s12888-019-2127-2) contains supplementary material, which is available to authorized users.

## Background

Borderline Personality Disorder (BPD) is one of the most common disorders in clinical settings. Psychotherapy is the primary treatment for BPD, with pharmacotherapy as an adjunctive treatment to target state symptoms [1]. In the last two decades, numerous psychotherapeutic approaches have been proposed for this diagnosis and their effectiveness in reducing symptoms and dysfunctions in behaviors seemed to be well supported, even though data on the improvement in social functioning is less optimistic [2–4]. Furthermore, these specialist treatments seem to have similar effects despite distinct theories and interventions. Moreover, despite progress, how psychological therapies produce this improvement is not fully understood [5]. Neurobiological studies could clarify the mechanism of change of psychotherapy for BPD and this could improve our knowledge of the pathophysiology underlying the disease. In particular, several MRI studies explored the neurobiological correlates of the disorder, showed volume reduction in amygdala and hippocampus [6–9], thickness decrease of the prefrontal cortex [10–12], and volume reduction in various regions of the temporal and parietal lobes [13, 14], as compared with healthy subjects. In the field of fMRI studies, the hyperactivity of the amygdala and hypo-activation of frontal areas in response to emotional stimuli in BPD samples [15] seems to be one of the most robust finding. These results were interpreted as the biological substrate of the core symptoms of the disease and, in particular, emotional dysregulation. The key question is whether psychotherapy is able to impact cerebral structures and functional activities and connectivity.

While the majority of the neuroimaging studies of psychotherapeutic treatments have been conducted on Axis I disorders, such as obsessive–compulsive disorder [15–18], mood disorders [19–21], panic disorder [22], social anxiety disorder [23], specific phobia [24, 25], and posttraumatic stress disorder (PTSD) [26], only a few studies explored the impact of psychotherapy in personality disorder and the most are in the context of Dialectical Behavioral Therapy for BPD. Goodman and colleagues showed BPD patients showed an overall decrease in amygdala after 12 months of DBT while the overall amygdala activation of the HC (healthy control) was comparable at baseline and 1 year follow-up [27].

A previous pilot study on 6 BPD patients showed comparable results, in particular a decreasing hemodynamic response to negative stimuli in the right-sided anterior cingulate, temporal and posterior cingulate cortices as well as in the left insula after a 12-week in-patient treatment program [28]. In another interesting study on a 12-weeks DBT program, patients exhibited reduced activity and increased connectivity in neural networks related to salience processing and emotion regulation after treatment [29, 30]. Preliminarily, some effects on brain structure, in terms of increased gray matter volumes in regions that are critically implicated in emotion regulation and higher-order functions, such as mentalizing, have been described [31].

Furthermore, Perez and colleagues [32] showed that after 1 year of Transference-Focused Psychotherapy [4] BPD patients showed relatively increased activation in dorsal prefrontal (dorsal anterior cingulate, dorsolateral prefrontal, and frontopolar cortices) in relation with treatment effect, and relatively decreased activation in ventrolateral prefrontal cortex and hippocampal after the intervention. Noteworthy, an increased left dorsal anterior cingulate cortex activation resulted positevely correlate to clinical improvement in constraint, while left posterior-medial orbitofrontal cortex/ventral striatum activation and negatively with right amygdala/parahippocampal activation seemed to be positively associated to clinical improvement in affective lability correlated. These results are very intriguing and they gave a great contribution to clarify possible mechanisms associated to clinical changes induced by the psychotherapy. No neuroimaging study has yet assessed the effect of other psychotherapy interventions on neurobiological features, e.g. approaches specifically oriented to increase mentalizing [3] or metacognition [33] that are often compromised in BPD and represent one of the core features in BPD patients. Metacognition, as conceptualized by Semerari [33], is the general capacity to think about thinking. Scarce metacognitive abilities have been associated to the difficulty to deal with interpersonal problems and deficit in using problem-solving strategies and choosing adaptive behaviors [34]. Metacognitive Interpersonal Therapy (MIT) is a cognitive behavior-based psychotherapeutic approach aimed to increase metacognitive abilities in order to improve general personality functioning and to promote better interpersonal relationships [35]. More in detail, MIT is designed to support patients in learning to recognize and integrate different mental states and in improving their ability to solve interpersonal problems using mentalistic knowledge of themselves and others.

The aim of the present study is twofold. The primary outcome will be the change in emotion dysregulation, measured by the Difficulties in Emotion Regulation Scale – DERS, [36, 37] after 12 months of MIT treatment in subjects with BPD. The secondary outcomes will be the effect of MIT on neurobiological (changes in cerebral patterns of activation in response to emotional visual stimuli during fMRI scans) and other clinical features. Lastly, we will study the correlation between patients’ metacognitive profiles and structural and functional brain imaging features.

## Method/design

### Trial design

The study design is a randomized parallel controlled clinical trial. For an overview of the proposed flow of participants, see Fig. 1. The present study protocol was written in accordance with the Standard Protocol Items: Recommendations for Interventional Trials (SPIRIT) [38]; copies of the SPIRIT Checklist and figure have been included in Table 1 and Additional file 1.

**Fig. 1 Fig1:**
[figure not shown]
Study Flowchart. MIT: Metacognitive Interpersonal Therapy; SCM Structured Clinical Management

**Table 1 Tab1:**
[figure not shown]
SPIRIT 2013 Figure for CLIMAMITHE study

*MIT* Metacognitive Interpersonal Therapy, *SCM* Structured Clinical Management, *SCID I-II* structured Clinical Interview for DSM disorder, axis I and axis II, *ZAN-BPD* Zanarini Rating Scale for Borderline Personality Disorder, *DERS* Difficulties in Emotion Regulation Scale, *MAI* Metacognitive Assessment Interview, *SCL-90-R* Symptoms Checklist-90- Revised, *BDI-II* Beck Depression Inventory. *TAS-20* Toronto Alexithymia Scale, *STAXI* State and Trait Anger Expression Inventory, *IIP* Inventory of Interpersonal Problems, *MRI-fMRI* Magnetic Resonance Imaging- Functional Magnetic Resonance Imaging

### Participants and study setting

Eighty BPD outpatients will be enrolled at 2 recruitment centres (IRCCS Istituto Centro San Giovanni di Dio, Brescia, Italy; Third Center of Cognitive Psychotherapy, Rome, Italy - Scuola Italiana di Cognitivismo Clinico-SICC, Rome). A group of 30 healthy volunteers will be enrolled as reference group IRCCS Istituto Centro San Giovanni di Dio, Brescia.

### Inclusion and exclusion criteria

The inclusion criteria for patients will be: age 18–45 and a diagnosis of BPD (DSM-IV-TR); informed consent. Patients will be excluded whether a lifetime diagnosis of schizophrenia, schizoaffective disorder, substance abuse or dependence in the 3 months before the enrolment, bipolar disorder, organic mental syndromes, dementia or cognitive impairment, relevant neurological signs will be ascertained. Furthermore, we will exclude pregnant women or lactating or patients receiving concurrent psychotherapy.

HCs will be represented by healthy volunteers without any cognitive impairment or psychiatric/neurologic condition, including alcohol/substance abuse.

### Clinical assessment

Independent expert psychologists will conduct the clinical assessment. Clinical evaluation are scheduled at the baseline, after 6, 12 (end of treatment), and 18 months.

The Structured Clinical Interview for DSM disorder [39, 40] will be used to define the diagnosis and collect data on comorbidities.

### Interventions

Patients will be randomly allocated to one of two interventions: Metacognitive Interpersonal Treatment (MIT) [35] or Structured Clinical Management (SCM) [1] delivered in each recruitment centre.

MIT is a cognitive behavioral-oriented psychotherapy designed to ameliorate metacognitive abilities and to enhance interpersonal relationships [35, 41, 42]. Metacognition pertain to a comprehensive set of cognitive and affective skills aimed to identify mental states, reasoning about them, and attributing them to themselves and others [33, 43]. These skills allow people to understand the reason why other persons react in such way, on the basis of own regularities and constructing personal meaning over their lifespan [44]. MIT is conceptualized to target the general psychopathology of personality. Treatment consists in 50-min one weekly individual session and a metacognitive skill training group (90 min) that cover a period of about 6 months during the year of the treatment. The MIT is manualized and follows a goal hierarchy, as proposed by the authors of the theoretical model [35]. In particular, the main goals of the treatment are: 1) the assessment of symptoms, mental state, metacognitive functions, interpersonal problems, emotion regulation skills; 2) intervention on the aspects that interfere with the therapeutic alliance and/or threaten the patient’s life (in particular, self-harming/suicidal behaviors); 3) intervention on symptoms that cause suffering to the patient; 4) intervention to promote the integration of different mental states MIT sessions will be supervised by the authors of the theoretical model through audio-record and the analyses of the narratives.

SCM is an evidence-based intervention that reflects “best general psychiatric treatment for BPD” and it’s feasible for use by “generalist mental health clinicians” with minimal additional training [45]. It was developed based on “expert consensus” about what general practices work best for treating this condition. SCM is the active comparator used in several study on BPD psychotherapy showing to be effective across an array of clinical outcomes [46]. SCM is tailored on BPD symptomatology and employs a supportive approach with case management and advocacy support. There is an emphasis on psychoeducation, problem-solving, explicit safety planning, medication review and assertive follow-up if appointments are missed. As the comparator, SCM treatment consists in 50-min one weekly individual session and a problem solving group (90 min) that cover a period of about 6 months during the year of the treatment.

Treatment retention was measured by the total number of weeks with at least one session and the number of weeks from the first to the last session attended. Patients were classified as having completed treatment if the time between the first and last sessions was at least 12 months between the 1st and the last session. Dropouts will be defined as those missing four consecutive sessions with no ascertained reason.

Treatment adherence. MIT therapists will be supervised throughout the duration of treatments, and treatment fidelity will be assessed using audiotaped sessions. For each therapist, 2 entire sessions will be recorded and evaluated by 2 senior therapists who developed the MIT, to ensure that the treatment is being done in a rigorous, reproducible, and similar way. As part of the assessment of fidelity, a treatment manual will be developed (as describe above). After each session, each MIT therapist will be required to fulfill a checklist on MIT strategies and techniques in order to monitor the fidelity. For SCM, bimonthly supervision will be mandatory to monitor the case management.

### Therapists’ requirements

Psychotherapies will be delivered by 12 “expert therapists”, with 4-year training in psychotherapy (psychodynamic- or CBT-oriented), a minimum of 2 years of clinical experience and a minimum of 1 year of experience treating BPD patients. More specifically, MIT therapists involved in the project will have received an intensive training in MIT (48 h), 4 years with Cognitive Behavioral are required. For SCM therapists, a 16 h-training on SCM will be delivered, no specific theoretical model will be required but expertise in treating BPD.

In each arm, patients will be randomly assigned to therapists within 2 weeks from the randomization.

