### Sample size

We consider as primary outcome the DERS score and assume quite homogenous population in terms of DERS scores among the recruitment centers. Previous studies reported that the standard deviation (SD) of DERS was 20.7 in females and 18.8 in males [36]. Thus, we assumed a SD of about 20 points. In addition, the correlation between two evaluations (12 months apart) was expected around 0.7 (indicating that about 50% of the variance of the second measurement should be explained by the first measurement). We computed that the SD of DERS changes will be about 15. Our hypothesis is that MIT will decrease DERS more than SCM and, more precisely, a difference between MIT and SCM mean effect larger than 10 points will be considered clinically relevant. To recognize such difference as statistically significant (at bilateral alpha level of 0.05) with an adequate power (0.80), the total number of patients to be recruited should be 60, raised up to 80 (40 MIT + 40 SCM), considering an attrition rate around 20%.

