### Statistical analyses

An evaluation of type of missing data will be performed in order to detect any missing not-at-random outcome data. A subsequent data-imputation technique (Bayesian imputation) will be applied to obtain complete outcome data. Descriptive statistics will be carried out with parametric and non-parametric tests accordingly to probability data distribution. The analyses of correlation between metacognitive profiles and specific clinical and morphological brain features (i.e. cortical thickness, regional volumes) will be assessed by linear and/or generalized linear models. For longitudinal analyses we will adopt the generalized linear mixed model or generalized estimating equation (GEE) models based on the covariance structure of the data. Lastly, to identify possible predictors of response, we will adopt logistic regression models where clinical and brain markers will be the covariates and the treatment response will be the dichotomous outcome.

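### Patients are nested in 12 therapists, and in therapy groups, within arm, but the sample size makes no allowance for this and the planned longitudinal model names no therapist or group level

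*Protocol article*

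**What the plan says.** **Therapists.** Under Therapists' requirements: "Psychotherapies will be delivered by 12" experienced therapists. MIT therapists need a cognitive behavioural background and 48 hours of MIT training; SCM therapists receive 16 hours of SCM training and need no particular theoretical model. Patients reach their therapist after randomisation: "In each arm, patients will be randomly assigned to therapists within 2 weeks from the randomization". The section mentions no therapist who works in both arms, and it does not give the split of the 12 between arms.

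**Groups.** Under Interventions, each arm adds a group component lasting about six months: "a metacognitive skill training group (90 min") for MIT and "a problem solving group (90 min") for SCM. Group sizes and numbers of groups are not given.

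**Sample size.** The test is two-sided ("at bilateral alpha level of 0.05") and planned "with an adequate power (0.80"). The target is stated thus: "a difference between MIT and SCM mean effect larger than 10 points will be considered clinically relevant". The other inputs are an SD of 20, a correlation of 0.7 over 12 months, an SD of change of about 15, and 60 patients raised to 80 for attrition of about 20%. The only homogeneity assumption concerns the two centres.

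**Analysis.** For longitudinal data the Statistical analyses section offers a generalized linear mixed model or "generalized estimating equation (GEE) models based on the covariance structure of the data". It names no random effect and no cluster unit.

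**The concern.** Patients who share a therapist, or sit in the same group, tend to have correlated outcomes. Because therapists belong to one arm only, the MIT versus SCM contrast is also a contrast between two small sets of therapists. Variation between therapists therefore enters the treatment difference and is not removed by comparing patients under the same therapist. A model that handles only the repeated DERS measurements of each patient captures the correlation within patients and leaves this second layer in the error. With few therapists per arm, one or two unusually strong or weak ones could then be mistaken for a treatment effect on the primary outcome.

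**Working it through.** **The plan's own figure.** With independent patients, a difference of 10, SD 15, two-sided 5% and 80% power, n per arm = 2 × (1.96 + 0.84)² × 15² / 10² = 35.3, so 36 per arm and 72 in total. The stated 60 is not reproduced. An SD of 15.49 (20 × √(2 × 0.3)) gives 76, and a baseline-adjusted SD of 14.28 gives 66. That gap exists before any clustering and is a separate matter. What counts here is that none of the stated inputs is a clustering term.

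**Inputs from the protocol article.** 80 patients; 20% attrition, so 80 × 0.80 = 64 evaluable; 12 therapists; difference 10; SD 20; correlation 0.7. The baseline-adjusted SD is 20 × √(1 − 0.7²) = 14.28.

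**Assumptions, not in the document.** 6 therapists per arm; equal caseloads; therapist ICC of 0.02 to 0.10.

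**Formulas.**
- Caseload m = 64 / 12 = 5.33.
- Design effect DE = 1 + (m − 1) × ICC.
- True two-sided error of a test that ignores therapist = 2 × (1 − Φ(1.96 / √DE)).
- Correct interval width relative to the naive one = √DE.
- Standard error of the difference = 14.28 × √(2/32) × √DE = 3.57 × √DE. Power comes from the noncentral t distribution with noncentrality 10 / SE.

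| ICC | DE | Type I error if therapist omitted | Width ratio | SE | Power, patient-level df (61) | Power, therapist-level df (10) |
|---|---|---|---|---|---|---|
| 0 | 1.00 | 5.0% | 1.00 | 3.57 | 78.7% | 71.4% |
| 0.02 | 1.087 | 6.0% | 1.04 | 3.72 | 75.3% | 67.8% |
| 0.05 | 1.217 | 7.6% | 1.10 | 3.94 | 70.5% | 63.0% |
| 0.10 | 1.433 | 10.2% | 1.20 | 4.28 | 63.4% | 56.1% |

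The 61 df are 64 patients less two arm means and a baseline slope; the 10 df are 12 therapists less two arms.

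**Check by simulation.** With 6 therapists per arm, 64 evaluable patients, SD 14.28 and 40,000 runs per setting, the patient-level test had type I error of 6.0%, 7.5% and 10.3% at the three non-zero ICCs. A test on therapist means held 4.9% to 5.0%. Once therapist is in the analysis, the cost is therefore power and not type I error.

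**Reading the power columns.** The first isolates the design effect. The second adds the smaller degrees of freedom of a test on 12 therapists, which costs about 7 points even at ICC 0 (78.7% against 71.4%). The two losses should not be added together and called clustering.

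**Sensitivity.** At ICC 0.01 with 64 patients the error is only 5.5%. If all 80 are analysed (m = 6.67), it is 6.3%, 8.4% and 11.7% at ICC 0.02, 0.05 and 0.10. The group component is not sized, because no group sizes are given.

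**The case against.** **The analysis is not described as treating patients as independent.** A reader might infer from the silence on therapists that it does, and so that the error rate is above 5%. The document does not support that. A generalized linear mixed model can carry a therapist effect, and the section names no random effects of any kind. Inflation needs two things that are not established: an ICC above 0 and a final model without therapist. This objection stands, and the point is conditional for that reason.

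**Random-effect levels are detail for an analysis plan.** This is a condensed article, and the choice of random effects, df method and ICC reporting could sit in a document not shown. That is fair for the model specification alone. It does not cover the sample size, which is set out with its inputs and has no clustering term; a later analysis plan cannot change how the number was reached. Nor does it fully cover the choice between mixed model and GEE, since a sandwich GEE clustered on only 12 therapists is unreliable.

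**The design limits therapist variation.** Patients are randomly assigned to therapists, therapists must meet experience and training minimums, MIT is manualised and fidelity-checked, and SCM has compulsory supervision. These measures may place the ICC towards the low end of the range. Random assignment prevents selective caseloads but does not remove correlation created by sharing a therapist, and nothing in the document shows the ICC to be zero.

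**The power loss can be overstated.** A reader might set the 56% to 68% at 10 df against 79% and blame clustering for the whole gap. Part of that gap comes from the choice of a 10-df test, as the table shows.

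**Conclusion.** The point holds in conditional form. The nesting is part of the trial's own design, the sample size makes no allowance for it, and the stated longitudinal model names no level that would absorb it. If therapist is omitted and the ICC is positive, the nominal 5% becomes about 6.0%, 7.6% and 10.2% at ICC 0.02, 0.05 and 0.10, and naive intervals should be 4%, 10% and 20% wider. Power for 10 points falls from 79% to about 75%, 70% and 63% through the design effect alone, or from 71% to about 68%, 63% and 56% if tested on 10 therapist-level df. These sizes rest on an assumed ICC range, an assumed 6 + 6 split, equal caseloads and 64 evaluable patients. The added effect of shared groups is left unquantified. This should be corrected, but it does not show that the trial's error rate is in fact inflated.

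**What to change.** 1. For the primary DERS analysis, choose the mixed model over GEE. Include a random therapist intercept nested in arm, with Kenward-Roger or Satterthwaite degrees of freedom.
2. Add therapy group as a sensitivity term.
3. Record therapist and group identifiers for every patient.
4. Report the estimated therapist ICC. With 12 therapists it will be imprecise.
5. State in the Sample size section that the 0.80 power ignores therapist clustering, and give the range above for ICC 0.02 to 0.10 with its assumptions.

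The cost is two extra data fields, one extra term in the primary model, a wider interval and a lower stated power. No change in enrolment is needed.
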